### Physical measurements

Anthropometric measurements are performed on each participant at each study visit. Weight is measured with the patient standing and then registered after rounding it to the nearest 500 g. Height is measured using a metric tape with the patient standing against a wall, and the value is marked by a ruler placed horizontally on the vertex of the patient’s head. Blood pressure is taken using an automated sphygmomanometer after a 5-minute rest in sedentary body position. Core temperature is taken using a tympanic membrane thermometer.

### Procedures for assessing coronary flow reserve with PET

#### Image acquisition

Patients will be asked to abstain from methylxanthine derivatives, including caffeine, for ≥ 24 h before ^13^N-ammonia PET scan acquisition. Vasodilator medications such as nitrate, β-blockers or calcium channel blockers will be stopped 24 h before PET scan acquisition.

PET imaging will be performed using a Discovery 710 PET-CT scanner (GE Healthcare, Waukesha, WI, USA). An intravenous bolus injection of 550 MBq of ^13^N-ammonia will be given for both stress and rest image acquisition. A total of 47 transaxial slices will be reconstructed over an axial FOV of 15 cm. The acquired PET pixel size is 2.73 × 2.73 × 3.27 mm. A CT scout projection determines the heart position within the patient, and low-dose cine CT (100 kV, 10 mA, 0.5 second/rotation, 40-mm collimation, 5.5-second duration) will be used for attenuation correction of PET data. The PET acquisition consists of a series of dynamic scans from 0 to 6 minutes (12 × 10 seconds, 6 × 20 seconds and 2 × 60 seconds) followed by a single 20-minute gated static scan. Approximately 30 minutes after completion of rest imaging, stress imaging will be performed with adenosine (140 μg/kg/minute) infused intravenously for at least 3 minutes before tracer injection. CT-based attenuation correction will be repeated for the stress study.

#### Myocardial blood flow and coronary flow reserve

PET images will be reconstructed using an iterative ordered subsets expectation maximisation algorithm (2 iterations, 24 subsets), and absolute myocardial blood flow will be quantified with a commercially available software tool (SyngoMBF; Siemens Medical Solutions, Hoffman Estates, IL, USA). The software automatically determines the arterial input and myocardial uptake functions and calculates total and segmental perfusion using the model of DeGrado et al. [17]. Total and regional CFR of the three main coronary territories (left anterior descending, left circumflex and right coronary arteries) will be computed.

The above methodology will be used to assess CFR at baseline and after 24 weeks of therapy. The CFR is expected to increase following CXCR2 inhibition as compared with placebo.

### Procedures for assessing coronary restenosis and plaque composition

#### Image acquisition

Angiography and IVUS imaging will be performed after administration of 200 μg of intracoronary nitroglycerine. Angiography will be performed so that each vessel is viewed from at least two orthogonal angles after the planned PCI. For the IVUS procedure, a 45-MHz, 3.2-French, rotational IVUS catheter (Revolution; Volcano Corp.) will be used. After the IVUS catheter is placed in the distal vessel, the catheter will be pulled back to the aortic ostium using the motorised pull-back system at 0.5 cm/second. During pull-back, greyscale IVUS will be recorded and displayed in real time, and raw radiofrequency data will be captured at the top of the R wave for post-procedural reconstruction of the colour-coded map by a VH-IVUS data recorder (s5 Imaging System; Volcano Corp.).

#### Greyscale and VH-IVUS analyses

The smallest lumen at the area of percutaneous intervention is identified from axial and longitudinal plaque distribution. At this site, vessel cross‐sectional area (CSA) will be calculated. The degree of restenosis will be assessed at 24 weeks by IVUS to measure minimum luminal CSA. This will be measured during the baseline PCI and again following 24 weeks of therapy. The degree of restenosis is expected to be reduced after 24 weeks of treatment with CXCR2 inhibition.

Atherosclerotic coronary plaques are characterised by classification trees on the basis of mathematical autoregressive spectral analysis of IVUS back‐scatter data (echoPlaque 4; INDEC Systems, Los Altos, CA, USA). Fibrous areas are marked in green, fibrofatty in yellow, dense calcium in white and necrotic core in red on the reconstructed colour‐coded tissue map. The area and percentage area of each plaque component in the tissue map are calculated automatically using echoPlaque software.

Measurements are made for the entire length of vessel that VH-IVUS images are acquired. The volume of vessel and each plaque component is calculated using Simpson’s method and averaged over the length of the lesion to also generate a mean plaque area. Plaque composition will be assessed at baseline and after 24 weeks of therapy by IVUS using the Volcano Corp. system to obtain virtual histology. Each coronary artery will have the total plaque volume recorded and percentage volumes of fibrous, fibrofatty, necrotic core and calcific tissue. We will assess the change in necrotic core volume between baseline and after 24 weeks of therapy. The percentage volume of necrotic core is expected to be reduced after 24 weeks of treatment with CXCR2 inhibition as compared with placebo.

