### Participant timeline

If eligible, subjects are scheduled for the following study visits (Fig. 1). Patients undergo invasive coronary angiography with PCI as per normal clinical care, but they will also undergo IVUS to provide greyscale and virtual histology of all major coronary arteries. Patients with suitable coronary anatomy will be invited to have invasive assessment of coronary and microvascular physiology under adenosine-induced hyperaemia (using a ComboWire; Volcano Corp., Rancho Cordova, CA, USA).

Four weeks later, subjects will re-attend the cardiology department, at which time a full history and physical examination will be performed and inclusion criteria confirmed. Assessments will include a 12-lead electrocardiogram, as well as blood tests (fasted) for blood count and biochemistry (renal, liver, lipid, glycaemic and thyroid profiles) and high-sensitivity C-reactive protein (hs-CRP) and homocysteine levels. Screening blood tests for disorders which may exclude patients from the study will be drawn as indicated (e.g., serum hepatitis B surface antigen, hepatitis C antibody, and HIV testing if prompted by history). Additionally, an aliquot of blood will be taken for measurement of circulating monocyte-platelet aggregates (MPAs, a highly sensitive and reproducible index of degree of platelet activation) by flow cytometry. In the case of women of childbearing potential, pregnancy will be excluded by performing a pregnancy test on a spot urine. Once eligibility has been confirmed, ^13^N-ammonia PET-CT cardiac scans will be obtained at rest and during adenosine-induced hyperaemia to measure CFR. The CT scan will be obtained prior to the PET scan for attenuation correction at rest and stress, and prior to the rest scan, the CT scan will also be used to measure calcium score.

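### Percentage necrotic core is measured over a vessel length that includes the PCI segment, so in treated arteries it is confounded with restenosis, in a direction and size the protocol does not fix

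*Protocol article*

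**What the plan says.** All participants have PCI of a native vessel (protocol, Inclusion and exclusion criteria). Participant timeline provides for "IVUS to provide greyscale and virtual histology of all major coronary arteries". Under the procedures for restenosis and plaque composition, Image acquisition starts with the catheter in the distal vessel, and then "the catheter will be pulled back to the aortic ostium using the motorised pull-back system".

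Greyscale and VH-IVUS analyses gives the region: "Measurements are made for the entire length of vessel that VH-IVUS images are acquired". It also says that volumes are "averaged over the length of the lesion to also generate a mean plaque area".

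The same section gives two necrotic-core metrics:
- Percentage: "Each coronary artery will have the total plaque volume recorded and percentage volumes of fibrous, fibrofatty, necrotic core and calcific tissue".
- Absolute: "We will assess the change in necrotic core volume between baseline and after 24 weeks of therapy".

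It states a directional expectation for each of two secondary endpoints:
- Plaque: "The percentage volume of necrotic core is expected to be reduced after 24 weeks of treatment with CXCR2 inhibition", with placebo as the comparator.
- Restenosis: "The degree of restenosis is expected to be reduced after 24 weeks of treatment with CXCR2 inhibition".

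Outcome measurements lists change in plaque composition and degree of in-stent restenosis as separate secondary endpoints. For plaque composition it names neither a metric nor a region.

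**The concern.** A pull-back from the distal vessel to the ostium crosses the treated site. If the whole length counts, tissue that accumulates in the stent between PCI and week 24 is added to total plaque volume. Percentage necrotic core in that artery can then move with no change in native plaque.

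Randomisation does not remove the problem, because the protocol expects the amount of in-stent tissue to depend on treatment. Two endpoints meant to answer different questions (is native plaque less inflamed, and is there less restenosis) become linked through a shared volume. A difference in percentage necrotic core, or the absence of one, could not be attributed to native plaque alone.

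The averaging sentence raises a smaller issue. A volume taken over the whole vessel and divided by the length of a lesion is a mean plaque area only if the two lengths coincide.

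**Working it through.** The protocol gives no SD, effect size or sample size for plaque composition, so there is no stated figure to reproduce. The check is a volume balance for one treated artery.

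**Inputs, all assumed because the document gives none**
- V: plaque volume at a post-PCI baseline.
- f0: necrotic-core share of that plaque.
- g: in-stent tissue added by week 24 (gP on placebo, gA on drug).
- fn: share of that added tissue coded as necrotic core.
- Native plaque does not change, unless stated.

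**Formulas**
- Percentage necrotic core at week 24 = (f0·V + fn·g)/(V + g).
- Shift from baseline = (fn − f0)·g/(V + g).
- Spurious drug-minus-placebo difference = (f0 − fn)·[gP/(V + gP) − gA/(V + gA)].

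If the drug limits regrowth (gA < gP), the bracket is positive, so the sign of the bias is the sign of f0 − fn.

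**Case V = 300 mm³, f0 = 20%, gP = 30, gA = 15 mm³**

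Bracket = 30/330 − 15/315 = 0.0909 − 0.0476 = 0.0433.

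| fn | Placebo shift (points) | Drug shift (points) | Drug minus placebo (points) |
|---|---|---|---|
| 0% | −1.82 | −0.95 | +0.87 |
| 5% | −1.36 | −0.71 | +0.65 |
| 20% | 0 | 0 | 0 |
| 35% | +1.36 | +0.71 | −0.65 |

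A positive difference is against the drug.

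**Range at fn = 0.** For V from 150 to 900 mm³, f0 from 15% to 25%, and regrowth of 30 versus 15 or 60 versus 30 mm³, the difference runs from +0.24 to +2.98 points.

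**A smaller assumed drug effect on regrowth.** With V = 420 mm³, f0 = 20% (84 mm³), fn = 0 and one third less regrowth on drug:
- 10 mm³ on placebo: 84/430 = 19.53% versus 84/426.67 = 19.69%, difference +0.15.
- 60 mm³ on placebo: 84/480 = 17.50% versus 84/460 = 18.26%, difference +0.76.

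**With a true drug effect.** Add a 10% relative fall in necrotic core on drug, still with fn = 0. Without in-stent tissue, V = 420 gives 75.6/411.6 = 18.37%, a fall of 1.63 points; V = 300 gives 54/294, the same fall.
- V = 420, 60 versus 40 mm³: 75.6/451.6 − 84/480 = 16.74% − 17.50% = −0.76 points.
- V = 300, 30 versus 15 mm³: 54/309 − 60/330 = 17.48% − 18.18% = −0.71 points.

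**Absolute necrotic core volume.** The spurious difference is fn·(gA − gP). It is 0 at fn = 0, so pure dilution does nothing. At fn = 35% with 15 versus 30 mm³ it is −5.25 mm³, in favour of the drug.

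**Untreated artery, or treated segment excluded at both time points.** g = 0, so the shift through this route is 0 for any V, f0 and fn.

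**The case against.** **The article is condensed, and frame selection belongs in a reading manual or the SAP.** This would answer a complaint that the text is silent. Here the article states a region, and that region contains the treated segment. A manual may exclude stented frames, but it would then depart from the published rule, and the two should agree.

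**The change to be assessed is an absolute volume.** This stands in part. The sentence just before the percentage expectation names necrotic core volume, which pure dilution leaves unchanged. But the directional expectation is on the percentage, and the endpoint list chooses neither.

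**The direction is unknown.** This stands. A reader might infer that the design necessarily works against the drug, or that success on restenosis would hide success on plaque. The document does not support either. It does not say how VH-IVUS codes in-stent tissue or struts. A low necrotic-core share is plausible for fibrous regrowth but remains an assumption. Even at a zero share, a true 10% relative fall is attenuated in the cases worked and keeps its sign.

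**The size is invented.** This also stands. No volumes and no SD are given, so the points above cannot be set against the endpoint's variability. Dosing starts only after the visit four weeks after PCI, so regrowth before then is not affected by treatment, which narrows any between-arm gap.

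**Baseline timing is open.** The article does not say whether the baseline VH-IVUS run precedes or follows stenting. The working assumes it follows. If it precedes, PCI itself also alters the measured segment, which is a further reason to leave it out.

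**The lesion-length average is only an additional measure.** Fair: it does not contradict recording whole-vessel volumes. The divisor still needs to match the region.

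**Conclusion.** The concern holds in a limited form. The stated region places the PCI segment inside the plaque-composition measurement of treated arteries, so percentage necrotic core there is confounded with restenosis, which the protocol expects to differ by arm.

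The bias is against an effective drug if in-stent tissue has a smaller coded necrotic-core share than native plaque, nil if the shares are equal, and in the drug's favour if the share is larger. Under the assumed inputs it is of the order of a few tenths of a point up to about 3 points. These figures are illustrative, and the true size cannot be derived from the document.

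Untreated arteries are unaffected. Absolute necrotic core volume is unaffected by dilution alone. The issue concerns a secondary endpoint and does not touch the primary CFR outcome. It should be corrected, because the correction works whatever the unknown inputs are.

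**What to change.** In the reading manual and SAP, and in the protocol wording on VH-IVUS analysis:

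1. Compute plaque composition, both percentage and absolute necrotic core, only on non-stented segments matched between baseline and week 24. Exclude the treated segment and a fixed edge margin at both time points.
2. Use the treated segment for the restenosis endpoint only.
3. Name one necrotic-core metric, percentage or absolute, as the secondary endpoint.
4. Reconcile the whole-vessel region with the lesion-length average, so that volumes and mean plaque area refer to the same length.

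The same images serve, and no extra procedure is needed. The cost is wording, to be settled before unblinding, and slightly less vessel length analysed.

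### The change in necrotic core volume is taken over whatever length was imaged at each visit, and the text does not say whether absolute or percentage volume is the endpoint

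*Protocol article*

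**What the plan says.** All the statements are in the protocol article.

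- **Length analysed** (Greyscale and VH-IVUS analyses): "Measurements are made for the entire length of vessel that VH-IVUS images are acquired".
- **Pull-back** (Image acquisition, under the procedures for restenosis and plaque composition): "After the IVUS catheter is placed in the distal vessel, the catheter will be pulled back to the aortic ostium". The proximal end is a fixed anatomical point. The distal end is not tied to a landmark or to the position used at baseline.
- **Quantity assessed** (Greyscale and VH-IVUS analyses): "We will assess the change in necrotic core volume between baseline and after 24 weeks of therapy".
- **Hypothesis** (same section): "The percentage volume of necrotic core is expected to be reduced after 24 weeks of treatment".
- **What is recorded** (same section): "Each coronary artery will have the total plaque volume recorded and percentage volumes of fibrous, fibrofatty, necrotic core and calcific tissue".
- **Averaged measure** (same section): vessel and component volumes are "averaged over the length of the lesion to also generate a mean plaque area".

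Outcome measurements lists the endpoint only as change in plaque composition by VH-IVUS. It is the first of three secondary endpoints.

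**The concern.** A volume obtained by integrating along a vessel depends on how much vessel is included. The two runs come from separate catheter procedures 24 weeks apart, and the stated rule takes in everything imaged on each occasion. A patient whose plaque has not changed can therefore show a fall or a rise in necrotic core volume because the second run started more proximally or more distally.

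The article also assesses one quantity (absolute volume) and predicts the behaviour of another (percentage volume). If the two disagree, the text does not say which of them answers the secondary objective.

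A smaller matter concerns the derived mean plaque area. A mean area is a volume divided by the length over which that volume was measured. Here the volume comes from the whole imaged length and the divisor is the lesion.

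What is at stake is precision and a clear reading of a secondary endpoint in a trial of 60 versus 30 patients. The primary PET endpoint is not affected.

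**Working it through.** The article gives no SD, expected effect or sample size for the VH-IVUS endpoint, so there is no stated figure to reproduce. The check integrates an unchanged plaque over different imaged lengths.

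**Assumptions (none is in the documents).** Baseline run 60 mm from the ostium; lesion 20 mm; *x* is distance from the ostium in mm.
- Uniform profile: plaque area 7 mm², 20% necrotic core throughout.
- Proximal-heavy profile: plaque area 9 - 4*x*/60 mm², necrotic core fraction 0.28 - 0.16*x*/60.

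**Formulas.** For imaged length *L*, with *U* = *L*/60:
- Uniform: necrotic core volume = 7 × 0.20 × *L* = 1.4*L*. Percentage = 20% for any *L*.
- Proximal-heavy: plaque volume = 60(9*U* - 2*U*²). Necrotic core volume = 60(2.52*U* - 1.28*U*² + 0.2133*U*³). Percentage is their ratio.

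**Results, disease unchanged.**

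| Repeat run | Uniform: volume (change) | Uniform: % core | Proximal-heavy: volume (change) | Proximal-heavy: % core |
|---|---|---|---|---|
| 66 mm | 92.4 mm³ (+10.0%) | 20.00 | 90.4 mm³ (+3.7%) | 20.15 |
| 60 mm | 84.0 mm³ (0) | 20.00 | 87.2 mm³ (0) | 20.76 |
| 54 mm | 75.6 mm³ (-10.0%) | 20.00 | 83.2 mm³ (-4.6%) | 21.40 |
| 48 mm | 67.2 mm³ (-20.0%) | 20.00 | 78.4 mm³ (-10.1%) | 22.06 |

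**Opposite directions.** In the proximal-heavy case at 54 mm, absolute volume falls by 4.6% while percentage volume rises by 21.40 - 20.76 = 0.64 points. The same unchanged plaque looks better on one measure and worse on the other.

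**Dividing by length is not enough on its own.** In the proximal-heavy case, volume per mm is 87.2/60 = 1.453 mm² at baseline and 83.2/54 = 1.541 mm² at the repeat, a rise of 6.0%, because the low-plaque distal end has been dropped. The segment has to be matched as well. If both runs are cut to the common 54 mm, volume (83.2 mm³), percentage (21.40) and volume per mm (1.541 mm²) are the same at both visits and the artefact is zero.

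**Is a 6 mm difference far-fetched?** The stated pull-back speed is 0.5 cm/s, with one radiofrequency frame per R wave. At an assumed 60 beats/min, frames are 5 mm apart; at 50 and 80 beats/min they are 6.0 and 3.75 mm apart. A 6 mm difference is therefore one to two frames.

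**Mean plaque area, read literally.** Plaque volume over 60 mm is 420 mm³. Divided by a 20 mm lesion it gives 21.0 mm²; divided by the length measured it gives 7.0 mm². This ratio does not enter the necrotic-core change.

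**The case against.** **Matching may be specified elsewhere.** The article condenses a fuller protocol, frame matching commonly sits in an imaging manual, and the statistical analysis plan is to be published separately. A bare omission would not be worth raising. What stands is that the article states a rule, the entire imaged length, and that rule followed as written does not give a matched segment.

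**The percentage measure is largely protected.** This is right. It does not move under a uniform profile and moves 0.64 points at 54 mm under the proximal-heavy one. The exposure is mainly in absolute volume, which is the quantity the article says it will assess.

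**The mean-area wording may just be loose.** The word lesion could stand for the analysed plaque, or the average could be lesion volume over lesion length. Either is possible, and the mean area is not a listed endpoint. A fixed ratio between the two lengths would also cancel in a percentage change. The sentence needs clarifying; nothing more follows from it.

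**Stronger readings that a reader might infer.**
- That the lesion divisor distorts the necrotic-core endpoint. It does not: it is used only for the derived mean area.
- That volume changes in exact proportion to imaged length. That holds only if necrotic core area is constant along the vessel; otherwise the change can be about half as large, as the -4.6% shows.
- That the noise would overwhelm a drug effect. With no SD or effect size given for this endpoint, that cannot be shown.
- That the comparison between arms is biased. Treatment is randomised and invasive assessments are made blind to allocation, so length differences unrelated to treatment add variance to both arms.

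**Conclusion.** The point holds as a cheap and worthwhile improvement to a secondary endpoint. Under the stated method, the change in absolute necrotic core volume depends on where the catheter starts distally at each visit. For a 54 mm repeat of a 60 mm run the spurious change is -10.0% (uniform) or -4.6% (proximal-heavy); percentage necrotic core changes by 0 or about 0.6 points. These sizes rest on assumed lengths and profiles. The dependence on imaged length needs only that some necrotic core lies in the part of the vessel seen at one visit and not the other.

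Independently of any arithmetic, the text assesses absolute volume, predicts a fall in percentage volume, and does not name which is the endpoint. The mismatch in the mean plaque area is a separate wording fault with no bearing on the necrotic-core change. The documents do not support a claim of bias between arms or of a drug effect being masked.

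**What to change.** 1. For each artery, analyse the segment common to both visits, from the ostium to a distal landmark, such as a side branch, seen on both runs. Choose the landmark blind to allocation.
2. Divide every volume, including that behind the mean plaque area, by the length of that same segment. If a lesion-level average is wanted as well, restrict both volume and length to the lesion and define its limits once for both visits.
3. Name change in percentage necrotic core volume in the matched segment as the endpoint, in line with the stated hypothesis, and report length-normalised necrotic core volume as supportive.

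**Cost.** A wording change and off-line matching of recordings that the trial makes anyway; no added procedure for patients. Unmatched length is discarded, and arteries with no shared landmark are lost, so their number should be reported by arm. Matching is only as fine as the frame spacing, so some length error remains.
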